## Methods/design

An eight-week, three-arm parallel randomized controlled trial will be conducted in Auckland, New Zealand with a total of 51 eligible participants. The primary outcome is cardiorespiratory fitness at 8 weeks after randomization. We hypothesize that participants who receive a smartphone app will have greater cardiorespiratory fitness compared to the control group. Secondarily, we hypothesize fitness, physical activity levels, self-efficacy, enjoyment and psychological needs satisfaction will be greater in the immersive app group compared to the non-immersive app group at 8 weeks after randomization. We also expect that recruitment goals will be met, attrition will be low, and that we will be able to collect complete data on at least 80 % (41/51) of participants.

The protocol is in accord with the SPIRIT 2013 statement [52, 53], and the intervention is described according to the CONSORT-EHEALTH checklist [54]. See Additional file 1 for the complete checklist.

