Interested participants either initiate contact with the research team or their contact details are obtained from sign-up sheets delivered while visiting schools to present the study. During an initial telephone call, interested participants are screened for eligibility [56] and a study information sheet is either posted or emailed. A baseline assessment is scheduled for eligible participants within 4 weeks of the screening call. Parents/caregivers provide written informed consent for their child (14–15), while the child provides written assent. Those aged 16–17 years provide their own written informed consent. Participants will receive a NZ $30 gift card to a local shopping center as an incentive for participation and encourage completion of study measures. Incentives are not conditional on usage of the app. Moreover, participants will be told both apps will be provided (i.e. free of charge) at study termination, which is particularly important to meet the expectations of using physical-activity related apps of those in the control group in order to avoid high dropout rates. As adherence to the intervention is one of the outcomes of interest, no reinforcement strategies will be used to influence compliance.

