### Outcome assessments

Assessments are conducted at baseline and 8-week post randomization (see Fig. 2) at the University of Auckland clinics and sport grounds (duration 45 to 60 min, of which 10 to 15 min to complete self-reported measures). Baseline assessments involve an explanation of study procedures, signed consent and collection of participant-reported secondary outcomes, followed by physical measurements (height and weight) and a field test of cardiorespiratory fitness. Participants are then asked to wear an accelerometer for seven consecutive days. Randomization takes place at a subsequent visit to the participants’ home once baseline accelerometer data collection is completed.

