### Sample size

A total sample of 51 participants (17 per group) will provide 80 % power at 5 % level of significance (two-sided) to detect a minimal difference of 17 s in time to complete the one mile run/walk test at 8-week post randomization between the treatment groups. This has assumed a standard deviation of 15 s on the primary outcome, with adjustment for multiple comparisons. Based on normative data [57] for this population, the calculation assumes a mean baseline value of 10-min to complete the one mile/1.6 Km run/walk test. An improvement in the completion time of 78 s for this distance corresponds to a shift from the 25^th^ to the 50^th^ percentile in terms of cardiorespiratory fitness, which is considered a meaningful impact towards a more favorable cardiovascular profile.

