### Randomization and blinding

Following the baseline measurement, participants are randomized at a 1:1:1 ratio to one of three conditions. The randomization sequence was generated by the study statistician using a computer program in variable blocks (3 and 6), stratified by sex [58]. Allocation was concealed in consecutively numbered, opaque sealed envelopes. Given the nature of the intervention, participants are aware of the group to which they have been allocated. The outcome assessor will not be blinded to the treatment allocation, however, the assessment of cardiorespiratory fitness and physical activity levels utilize objective measures.

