
### Statistical analyses

Treatment evaluation will be performed on the principle of intention to treat. Statistical analyses will be conducted using SAS version 9.3 software (SAS Institute, Cary, NC, USA). All statistical tests will be two-sided and maintained at a 5 % significance level. Apart from accelerometry, study data will be keyed into an Excel database using data forms enabled with validation criteria. An assistant will randomly check 30 % of the keyed data for accuracy. All data will be imported into SAS for final analysis.

Baseline characteristics of all randomized participants will be presented for each group using descriptive statistics. Continuous variables will be reported as numbers of observed and missing values, mean, standard deviation, median and range. Categorical variables will be described as frequencies and percentages.

Analysis of covariance (ANCOVA) regression model will be used to evaluate the main treatment effects on the primary outcome, adjusting for its baseline measure, sex, and important baseline confounding factors. Normality of the continuous outcome data will be tested, and the goodness of model fit will be evaluated. Model-adjusted means will be estimated for each group, and their differences will be tested. A similar approach will be used for other continuous secondary outcomes. Generalized linear models will be applied to categorical outcomes as appropriate. Sensitivity analysis will be conducted on the primary outcome with missing data (if >10 %), using multiple imputations with the MCMC method [82].

Psychosocial variables (i.e. perceived enjoyment, autonomy, competence, relatedness and self-efficacy) related to physical activity will be considered as potential mediators of the intervention (Fig. 5 illustrates the mediation model to be tested; dotted lines indicate hypothesized mediation paths) [83]. The recommendations of Kraemer for testing mediators of intervention effects in randomized clinical trials will be followed [83]. Data permitting, further analyses will evaluate the treatment effects on a subgroup of participants who report having adhered to the intervention.

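### The stated missing-data check runs only above 10 % missing and shares the missing-at-random assumption of the ANCOVA, so it cannot reveal bias from outcome-dependent dropout

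*Protocol article*

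**What the plan says.** All references are to the protocol article.

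- **Statistical analyses, main model:** "Analysis of covariance (ANCOVA) regression model will be used to evaluate the main treatment effects on the primary outcome, adjusting for its baseline measure, sex", with other baseline confounders also adjusted for. How the model treats a participant without an 8-week time is not stated.
- **Statistical analyses, principle:** "Treatment evaluation will be performed on the principle of intention to treat".
- **Statistical analyses, missing data:** "Sensitivity analysis will be conducted on the primary outcome with missing data (if >10 %), using multiple imputations with the MCMC method". No imputation model or auxiliary variable is named, and the base of the 10 % (all participants, or each arm) is not given.
- **Outcome assessments:** "Assessments are conducted at baseline and 8-week post randomization". There is no interim visit.
- **Methods/design:** the authors expect that "we will be able to collect complete data on at least 80 % (41/51) of participants", which tolerates up to 10 of 51 incomplete (19.6 %).
- **Randomization and blinding:** "participants are aware of the group to which they have been allocated".
- **Study sample and recruitment:** both apps are promised at study end to "meet the expectations of using physical-activity related apps of those in the control group in order to avoid high dropout rates".

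**The concern.** A sensitivity analysis is useful when it relaxes the assumption that the main analysis rests on. Here both analyses rest on the same one: given arm and baseline covariates, those who do not return would have run like those who do.

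That is open to doubt in this trial. Allocation is known to participants, and the outcome is a best-effort mile run that requires a return visit. Someone who stopped training, or who expects a poor time, has a reason not to come. If this happens unevenly between arms, the estimate is biased, and the planned check would agree with it. The report could then describe a result as robust to missing data on evidence that cannot show it.

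The 10 % trigger adds a smaller problem. At low counts no check is run, although in arms of 17 a handful of absences is a sizeable share of one arm.

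**Working it through.** **1. The plan's own figure.** Inputs from the Sample size section: difference 17 s, SD 15 s, 80 % power, two-sided 5 %, adjusted for multiple comparisons. Taking the adjustment as 0.05/3 (the method is not named):

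n per arm = 2 (z₁₋α/₂ + z₀.₈)² (SD/difference)² = 2 × (2.394 + 0.842)² × (15/17)² = 16.3, so 17 per arm and 51 in total.

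The stated number reproduces. So 17 s and 15 s are the right scale to start from.

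**2. The trigger, read as pooled.** 10 % of 51 = 5.1. Five missing is 5/51 = 9.8 %: no check. Six is 6/51 = 11.8 %: check. Five missing could be as much as 5/17 = 29 % of one arm.

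**3. Why imputation returns the ANCOVA answer.** Let b be the least-squares fit to the observed times. Imputation under missing at random, from the same covariates including arm, fills each gap with x·b on average. Each filled point then lies on the fitted surface, so refitting the ANCOVA gives b again, apart from simulation noise. Only variables outside the ANCOVA could change this, and none are named.

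**4. Stress-case simulation.** Three arms of 17, normal outcome, true effect 0, covariates baseline time and sex, the slowest 8-week times in one app arm missing. 2,000 trials per row, 50 imputations each, drawn from the posterior of the normal regression. The baseline correlations are assumptions. The SD of 116 s is also assumed: the Sample size section puts 78 s between the 25th and 50th percentiles, and under normality 78/0.674 = 116 s.

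| SD (s) | Baseline correlation | Missing in arm | Full data (s) | Observed-case ANCOVA (s) | Imputation (s) |
|---|---|---|---|---|---|
| 15 | 0 | 5 | 0.0 | -6.9 | -6.9 |
| 15 | 0.5 | 5 | 0.2 | -5.2 | -5.2 |
| 15 | 0.7 | 5 | 0.2 | -3.6 | -3.6 |
| 15 | 0.9 | 5 | 0.1 | -1.4 | -1.4 |
| 116 | 0.8 | 5 | 0.2 | -20.8 | -20.8 |
| 15 | 0.5 | 6 | 0.1 | -6.2 | -6.3 |
| 116 | 0.8 | 6 | 0.5 | -24.2 | -24.1 |

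The last two rows matter most: with six missing a pooled trigger is met, the check runs, and it agrees with the biased result. A harsher rule, removing the five with the worst time relative to their own baseline, gives -3.0 to -7.1 s at SD 15 s and -31.2 s at SD 116 s, again the same for both methods.

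**5. Size without simulation.** If the missing share of an arm is p and the missing times are d seconds slower than predicted, the arm mean is off by about p × d. With p = 5/17:

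- d = 15 s gives 4.4 s
- d = 30 s gives 8.8 s
- d = 58 s gives 17 s (17 ÷ 5/17 = 57.8)
- d = 78 s gives 22.9 s

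A shift of 57.8 s is 57.8/15 = 3.9 SDs on the protocol's scale. At SD 116 s and correlation 0.8 the residual SD is 116 × 0.6 = 69 s, and the same shift is about 0.8 of it. The answer depends heavily on which SD is realistic.

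**The case against.** **The text is a condensed article.** A fuller analysis plan may hold the imputation model, auxiliary variables and further analyses. A reader might infer that no other missing-data analysis exists; the article does not say so, and its silence is not an exclusion. What stands is that the article fixes one rule, with a trigger, and that rule followed as written does not test the assumption in question.

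**Imputation under missing at random is legitimate.** True, and it should stay. Nor does it follow that the check is blind to all dropout bias. Baseline accelerometry, questionnaires and body mass index are collected, as are 8-week questionnaires from anyone who attends but does not run. Used as auxiliary variables, they could expose dropout bias related to them. The limit applies to dropout that depends on the unobserved time after what is in the model.

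**The ANCOVA may not drop anyone.** A reader might infer that it does. The article commits to intention to treat and leaves the handling of missing times open. An ANCOVA as described can use only observed times, but that is an inference.

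**The trigger may be by arm.** Then 5 of 17 in one arm would set it off, and the example of a whole arm's dropout escaping notice disappears. On the pooled reading, if dropout were unrelated to arm, the chance that five missing all fall in one arm is 3 × C(17,5)/C(51,5) = 0.8 %. At the tolerated 10 of 51, a pooled trigger would be met if the missing data were run times. So the trigger is the lesser half of the point.

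**The scenario is severe and one-sided.** It removes exactly the slowest five, all from one app arm. The article's own stated worry is control-arm dropout, and it offers a gift card and both apps at the end to reduce losses. This is why the fix must cover both directions.

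**Conclusion.** The point holds in limited form, as a cheap improvement. The stated check rests on the same assumption as the analysis it accompanies. With two assessments and no auxiliary variables named, it returns nearly the same estimate, so it cannot reveal bias from dropout that depends on the 8-week time. This applies whether or not the trigger is met. The trigger also leaves low counts unchecked, and its denominator is undefined.

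In the stress case the undetected bias is about 1 to 7 s at the protocol's SD, under half of the 17 s target. It is about 20 s if the SD is near 116 s. The second figure rests on normality and a correlation of 0.8, neither of which the article gives. A reader might take 20 s as the expected bias; it is not a forecast, and nothing in the article shows that dropout will follow this pattern. The equality of the two methods assumes that the imputation model uses the ANCOVA's own covariates.

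**What to change.** In Statistical analyses:

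1. Delete the 10 % trigger and run the sensitivity analysis whenever any 8-week time is missing.
2. Report the number missing, with reasons where known, by arm.
3. State how the main ANCOVA treats missing times. Keep the multiple imputation, and name its variables, including any from outside the ANCOVA.
4. Add a delta-adjusted tipping-point analysis. After imputing under missing at random, add a fixed shift to the imputed times, set separately for the app arms and the control arm, over a stated range that includes 17 s (for example 0, 17, 34, 51 and 78 s). Use both signs in the control arm, since slower or faster missing controls move the comparison in opposite directions. Report the shift at which the conclusion changes.

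The cost is a little more code after an imputation step already planned, and one more table. The Trial status section says follow-up is complete and analysis ongoing, so no data collection changes. The addition should be dated, and labelled as added late if results by arm have already been seen.

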**Fig. 5 Fig5:**
[figure not shown]
Mediation model to be tested (dotted lines indicate hypothesized mediation paths)

## Discussion

The AIMFIT study aims to investigate the effectiveness of two commercially available smartphone applications to improve fitness and activity levels in young people. While there is considerable potential for enhancing the reach of behavior change interventions through the use of smartphone apps, their effectiveness as a stand-alone approach is yet to be determined. This randomized controlled trial will provide much needed data regarding the effectiveness of an off-the-shelf intervention involving minimal contact with the participant to promote fitness and physical activity in young people.

A pragmatic study design was chosen because we were interested in evaluating the effects of the apps in a real or everyday routine [84]. The AIMFIT participants use the app at locations and times of their choice where app utilization tends to occur, which will maximize the findings’ ecological validity. The intervention and its delivery are allowed to vary (e.g. different devices, different utilization of the apps), respecting the participants’ decisions, and no additional efforts will be made for its standardization. While we recognize this limitation, the present study will provide insights of the usefulness of the intervention in a real world setting where it would be implemented, thereby increasing the applicability and generalizability of the results [85]. Although frequency and duration of self-initiated use of the apps will neither be directly observed nor reported by the participants during the intervention, those in the experimental groups will self-report frequency of app use at study completion on the exit survey, which, despite prone to recall and social desirability bias, is a relevant outcome per se. Co-interventions (i.e. intervention groups access other apps) and/or contamination (i.e. control group accesses the apps under investigation) are a limitation of this design. However, and importantly, we were targeting a young population (i.e. 14–17 years) and the apps under investigation were paid, not free. While not expensive, purchasing an app on an app store requires a credit card, which young people do not typically own.

In the current study we will investigate apps readily available for the public/consumer to purchase, rather than apps designed by the research team. This approach has caveats in that we are limited to the decisions made by the app developers, such as the content of the app, duration of the training program, and other design features. The research team is unable to objectively access data on app usage (e.g. which and when features are used) as we would have had we programmed our own app. Moreover, the short duration of the chosen intervention precludes investigation of long-term effects.

The apps herein investigated were designed to promote fitness through an eight-week progressive training program based on walking, brisk walking, and running. Arguably, running may not be as easily incorporated in daily life activities as compared to walking, and therefore be less sustainable in the long-term. However, we were interested in the effectiveness of these commercially available apps and running is more likely to promote short-term effects in fitness than walking alone would. Additionally, promoting a more intense aerobic activity (i.e. running) will likely be perceived as an “exercise activity”, and intervention features that attempt to make this activity more immersive, and consequently engaging, is the purport of one of the apps under investigation. The AIMFIT study design and proposed interventions reflect these considerations and the target population. One of the strengths of the study is the objective measurement of the main outcome and of physical activity using accelerometers. Despite its shortcomings, this trial will provide valuable insight into the effects of using a non-immersive “workout context” app or an immersive “gaming context” app to improve fitness and physical activity. Moreover, secondary outcomes will be measured to determine the impact of the intervention on behavior and psychosocial processes. Physical activity levels and psychosocial variables (i.e. self-efficacy, enjoyment and psychological needs satisfaction) will be assessed to determine their potential mediating effects. The presence of mediating effects will indicate the ability of the apps to change physical activity behavior and/or psychological variables, which are underlying mechanisms through which the apps might achieve its effects on fitness.

The AIMFIT trial will also inform on important aspects such as recruitment, compliance, utilization of the intervention, retention, adverse events, and potential issues specific to the context of the research. These issues will be of interest and can provide guidance to those interested in mHealth in general and specifically to those conducting similar work.

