A proposed model for better understanding how an app intervention may influence possible mediators that change physical activity behavior and consequently improve fitness is presented in Fig. 1. It is hypothesized that the app will positively affect mediating variables, such as enjoyment, autonomy, competence, relatedness, and self-efficacy; which in turn would result in physical activity-related changes in fitness. We identified two commercially readily available apps, both designed to promote increases in walking and running, which are physical activity behaviors that contribute to improvements in fitness. Additionally, we are interested in comparing an app designed with an immersive story to an app without story since game-based stories that engage individuals can be used for health behavior change [24, 35] to model behaviors by immersing and capturing attention.

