#### Secondary outcomes

The following secondary outcomes are assessed at baseline and 8 weeks.Anthropometrics (body mass index) are measured using standardized practices [66]. Bodyweight is measured to the nearest 0.1 kg using a calibrated scale (Salter), while height is measured to the nearest 0.1 cm using a stadiometer (Seca). Physical measurements are taken as the average of two readings.Self-reported physical activity is assessed using the Physical Activity Questionnaire for Adolescents (PAQ-A), a validated self-report seven day recall measure with good internal consistency (Cronbach alphas range from 0.72 to 0.85) and acceptable validity compared to an activity monitor (rho = 0.49) [67]. The PAQ-A items assess physical activity at school (i.e. physical education, lunchtime), after school, and at home (organized and recreational). Each statement is scored on a five-point scale with higher scores indicating higher activity levels. The final PAQ-A score is an average of eight items [68].Objectively measured physical activity is assessed using the GT1M Actigraph (http://www.actigraphcorp.com), a motion sensor shown to be a valid and reliable instrument for assessing physical activity in young people [69]. Participants are asked to wear the Actigraph following each assessment for seven consecutive days. They are instructed to wear the monitor during waking hours on their mid-axilla line right hip, removing it when engaging in activities involving water (e.g. water sports, showering) and contact sports. Participants are asked to complete a daily log detailing the time the Actigraph was put on and removed.The GT1M model was initialized to collect data in 10-s epochs [70]. The ActiLife software (version 5) [71] is used to initialize the accelerometers and download the data following wearing periods. All accelerometer data files are exported individually as a .csv file and aggregated into a combined .csv file that is imported into SAS. During subsequent processing, data are aggregated into minute intervals. To determine valid wear time, periods of more than 60 min of consecutive zeroes and days with less than 600 min of valid records are removed before data analysis [72]. All participants with at least 3 days of valid data will be included in the analysis [73]. The average daily time spent in sedentary, light, moderate, vigorous and moderate to vigorous activities is calculated for each participant. The Evenson cut points for defining activity intensities are used: sedentary <100, light >100, moderate ≥2296, vigorous ≥4012 [74–76].Perceived enjoyment of physical activity is assessed using the Physical Activity Enjoyment Scale (PACES) [77]. Participants rate their agreement with 16 statements on a five-point Likert type scale (e.g. “When I am active it gives me a strong feeling of success”). Factorial validity and gender invariance among older adolescents has been previously demonstrated [78]. Scores are summed with higher scores indicating higher level of enjoyment.The Psychological Need Satisfaction in Exercise Scale (PNSES) [79] is used to measure perceived competence, autonomy and relatedness while exercising. Participants rate their agreement with 18 items on a six-point Likert type scale (e.g. “I feel free to exercise in my own way”). Six items are referenced to each of the three domains. Construct validity and gender invariance for the PNSES have been previously documented [79].Self-efficacy is assessed using the Physical Activity Self-Efficacy Scale (PASES) [80]. This eight item questionnaire has well-established validity [81]. Items are scored from on a 3-point Likert-type scale (e.g. “I can be physically active most days after school”), with a higher summed score indicating higher self-efficacy.Self-reported frequency of app utilization (e.g. “How many times per week did you use the app?”), acceptability (e.g. Will you continue to use the app?”), and usability (e.g. “When did you use the app?”) of the apps are assessed via an exit survey conducted with all intervention participants. A series of open-ended questions are asked to determine the features participants considered most and least acceptable, as well as the ones they used most often to support their physical activity. Objective data on app usage (i.e. automatically logged in the background while features were accessed) was not possible to collect due to the apps not being developed by the research team and not being open source (i.e., could not be modified to suit investigation purposes).

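### The schedule cannot support the mediator-to-fitness part of the mechanism claim: the psychosocial scales share the 8-week visit with the run test, and the accelerometer week follows it

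*Protocol article*

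**What the plan says.** The Background sets out a causal chain. The app acts on enjoyment, autonomy, competence, relatedness and self-efficacy, "which in turn would result in physical activity-related changes in fitness". The Statistical analyses section says that these psychosocial variables "will be considered as potential mediators of the intervention" and refers to Fig. 5 for the model. The Discussion adds physical activity levels to the list and states: "The presence of mediating effects will indicate the ability of the apps to change physical activity behavior and/or psychological variables". The same sentence describes these variables as the mechanisms by which the apps might achieve their effect on fitness.

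On timing, Outcome assessments says: "Assessments are conducted at baseline and 8-week post randomization". Each visit is a single session ("duration 45 to 60 min, of which 10 to 15 min to complete self-reported measures"). For baseline the order is given as "collection of participant-reported secondary outcomes, followed by physical measurements (height and weight) and a field test of cardiorespiratory fitness". Under Secondary outcomes, "The following secondary outcomes are assessed at baseline and 8 weeks", and for accelerometry "Participants are asked to wear the Actigraph following each assessment for seven consecutive days". The PAQ-A, the self-reported activity measure, is a seven-day recall completed at the visit.

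**The concern.** A claim that a variable carries the app's effect to fitness needs evidence that the variable changed before fitness did. Here the psychosocial scales are recorded at the same session as the 8-week fitness result, and objective activity is recorded after it. Adolescents who have become fitter may enjoy exercise more, feel more competent and move more in the following week. That would produce the same 8-week association as true mediation.

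At stake is a secondary conclusion: whether the report may say how the apps work. The Discussion lists other limitations, such as the lack of objective usage data and the short duration, but not this one.

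**Working it through.** **1. The plan's own figure.** The protocol gives no calculation for mediation. Its one design calculation (Sample size) uses a difference of 17 s, an SD of 15 s, 80 % power and a two-sided 5 % level with an unnamed multiplicity adjustment. Assuming Bonferroni for three comparisons (0.05/3):

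n per group = 2 × (2.394 + 0.842)² × (15/17)² = 2 × 10.47 × 0.7785 = 16.3, rounded up to 17, so 51 in total.

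This matches the protocol; power at 17 per group is 81.9 % by the same normal approximation. It is used here only for the standardized effect, d = 17/15 = 1.13.

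**2. The timeline.** Take the 8-week run test as day 0.

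| Measure | Period observed | Position relative to the outcome |
|---|---|---|
| Psychosocial scales | day 0, same session | simultaneous |
| Accelerometer | about day +1 to +7 | after |
| PAQ-A | recall of about day −7 to 0 | before, last week only, self-report |

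If the baseline order also holds at 8 weeks, the scales are completed shortly before the run. That does not help, because any change in fitness has built up over the preceding eight weeks.

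**3. What each path can show.**
- App to mediator: a randomized comparison, estimable from these data.
- Mediator to fitness: not randomized, and the order in time is not established. For accelerometry the observed order is the reverse of the Background chain.

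**4. Illustration of reverse causation.** Let X be app (34) or control (17). Let fitness be Y = dX + e and the mediator M = rY + √(1 − r²)·u, with e and u independent standard normal. M is then only a consequence of fitness, and true mediation is zero.
- Regressing M on X gives a = rd.
- Regressing Y on X and M gives b = r, since within arm Cov(Y, M) = r and Var(M) = 1.
- The apparent indirect effect is ab = r²d, a share r² of the total: 9 %, 25 % and 49 % for r = 0.3, 0.5 and 0.7. Sample size does not enter, so a larger trial would not remove the spurious effect.

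Mediation was declared when both paths reached p < 0.05, over 4,000 simulated trials per setting:

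| d | r = 0.3 | r = 0.5 | r = 0.7 |
|---|---|---|---|
| 17/15 = 1.13 | 12 % | 45 % | 74 % |
| 0.5 | 4 % | 13 % | 22 % |
| 0 | 2 % | 5 % | 5 % |

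The mean simulated indirect effects at d = 1.13 were 0.104, 0.280 and 0.547, against r²d = 0.102, 0.283 and 0.555. The correlations and the value d = 0.5 are assumptions, and the simulation makes no baseline adjustment.

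**5. The mediator lists.** The text of Statistical analyses names five psychosocial variables. The Discussion names physical activity levels as well.

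**The case against.** The best case for the plan has five parts.

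- *The sentence is partly sound and is hedged.* Its first half concerns whether the apps change activity or psychological variables, which the randomized comparison can test. The text also speaks of potential mediators and of what the apps might achieve. This stands for the app-to-mediator effect. It does not rescue the mechanism clause, because the presence of mediating effects is still said to indicate mechanism.
- *One activity measure does look back.* The PAQ-A recall week precedes the run test. This stands, so it would be wrong to infer that no candidate mediator is observed between randomization and outcome. Its value is limited: one week of eight, self-reported at the same visit.
- *Accelerometry may never be entered as a mediator of fitness.* The text of Statistical analyses names psychosocial mediators only, and Fig. 5 is not shown. This stands. A reader might infer that the formal plan commits to post-test accelerometry as a mediator; it does not say so. The concern arises because the Discussion names physical activity levels without saying which measure.
- *The psychosocial-to-activity link is in the right order.* Scales at the visit followed by a week of accelerometry fit that link in the Background chain. This stands, but the Discussion's claim extends to fitness.
- *The illustration assumes its answer.* It sets true mediation to zero and chooses the correlations. It shows that a false conclusion is possible and sometimes frequent, not that reverse causation is as likely as mediation. At d = 0.5 and r = 0.3 the rate is only about 4 %.

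**Conclusion.** The concern holds for the mediator-to-fitness inference in the Discussion. With the psychosocial scales taken at the outcome visit and accelerometry taken after it, the data cannot show that these mediators changed before fitness did. In the illustration a purely reverse association is declared mediation in between 4 % and 74 % of trials, depending on the assumed effect (0.5 or 1.13 SD) and correlation (0.3 to 0.7).

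The point goes no further than that. A reader might infer that the app effects on enjoyment, self-efficacy or activity cannot be tested, or that the main result is compromised. Neither follows: those effects are randomized comparisons, mediation is a secondary analysis, and the primary ANCOVA and the sample size are unaffected. The conclusion rests on the stated schedule. The order of measures within the 8-week visit is inferred from baseline, and Figs 2 and 5 could not be seen.

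**What to change.** Trial status says that follow-up is complete and analysis is ongoing, so no new measurement can be added. These changes to analysis and wording remain possible:

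- Report the arm effects on each psychosocial scale and on activity as randomized comparisons.
- Present mediator-fitness associations, adjusted for baseline, as exploratory and non-causal.
- In the Discussion, replace the mechanism inference with the limitation: the scales were taken at the outcome visit, and the accelerometer week followed it.
- Do not enter accelerometer activity recorded after the 8-week run test as a mediator of fitness. If activity is examined as a mediator, use the PAQ-A and state its limits (last week only, self-report, same visit).
- Make the mediator lists in the text of Statistical analyses and the Discussion agree.

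The cost is redrafting a few sentences and fixing the choice of activity measure. No sample-size figure or primary analysis changes. What is given up is the claim about how the apps work, which this schedule could not support.
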